# Immediate and short-term effects of continuous theta burst transcranial magnetic stimulation over contralesional premotor area on post-stroke spasticity in patients with severe hemiplegia: Study protocol for a randomized controlled trial

**DOI:** 10.3389/fneur.2022.895580

**Published:** 2022-08-23

**Keywords:** spasticity, stroke, premotor area, theta burst stimulation (TBS), H reflex, randomized controlled trial, diffusion tensor imaging (DTI)

## Abstract

**Background:**

Post-stroke spasticity is an important complication that greatly affects survivors' functional prognosis and daily activities. Increasing evidence points to aberrant contralesional neuromodulation compensation after brain injury as a possible culprit for increased spasticity in patients with severe stroke. Hyperactivity of the contralesional premotor area (cPMA) was supposed to be highly correlated with this progression. This study aims to demonstrate the immediate and short-term efficacy of continuous theta-burst stimulation (cTBS) targeting cPMA on upper limb spasticity in severe subacute stroke patients.

**Methods:**

This trial is a single-center, prospective, three-group randomized controlled trial. Forty-five eligible patients will be recruited and randomized into three groups: the sham-cTBS group (sham cTBS targeting contralesional PMA), the cTBS-cM1 group (cTBS targeting contralesional M1), and the cTBS-cPMA group (cTBS targeting contralesional PMA). All subjects will undergo comprehensive rehabilitation and the corresponding cTBS interventions once a day, five times a week for 4 weeks. Clinical scales, neurophysiological examinations, and neuroimaging will be used as evaluation tools in this study. As the primary outcome, clinical performance on muscle spasticity of elbow/wrist flexor/extensors and upper-limb motor function will be evaluated with the modified Ashworth scale and the Fugl-Meyer Assessment of Upper Extremity Scale, respectively. These scale scores will be collected at baseline, after 4 weeks of treatment, and at follow-up. The secondary outcomes were neurophysiological examinations and Neuroimaging. In neurophysiological examinations, motor evoked potentials, startle reflex, and H reflexes will be used to assess the excitability of the subject's motor cortex, reticulospinal pathway, and spinal motor neurons, respectively. Results of them will be recorded before and after the first cTBS treatment, at post-intervention (at 4 weeks), and at follow-up (at 8 weeks). Neuroimaging tests with diffusion tensor imaging for all participants will be evaluated at baseline and after the 4-week treatment.

**Discussion:**

Based on the latest research progress on post-stroke spasticity, we innovatively propose a new neuromodulation target for improving post-stroke spasticity *via* cTBS. We expected that cTBS targeting cPMA would have significant immediate and short-term effects on spasticity and related neural pathways. The effect of cTBS-cPMA may be better than that of cTBS *via* conventional cM1. The results of our study will provide robust support for the application of cTBS neuromodulation in post-stroke spasticity after a severe stroke.

**Clinical trial registration:**

This trial was registered with chictr.org.cn on June 13, 2022 (protocol version). http://www.chictr.org.cn/showproj.aspx?proj=171759.

## Introduction

Post-stroke spasticity is defined as a velocity-dependent increase in exaggerated stretch reflex responses due to the hyperexcitable descending excitatory brainstem pathways and results in the hyperexcitability of alpha motor neurons in the spinal cord (1). Spasticity is a common complication after stroke, with the prevalence ranging from 30% to 80% of stroke survivors (2). The appearance of spasticity after stroke can significantly affect the patient's recovery of motor function and cause long-term problems such as joint contractures, abnormal pain, and deformity (3). The spasticity of most patients with mild to moderate stroke will gradually improve during the movement recovery process, but that of some patients with severe injury will progress in the opposite way (4). Reorganization of the descending cortical spinal tract (CST) and reticular spinal tract (RST) from both hemispheres may be a plausible explanation for this distinct development (5).

Both CST and RST are the two important descending pathways of postural and motor control in primates. RST is usually considered to control proximal and axial muscles, and to be involved mainly in movement and posture adjustment, while CST is thought to be involved in fine motor control (6). The two tracts are competitive but in a wonderful state of balance. Significant brain lesion after stroke causes structural damage to these descending pathways, especially in the compact pyramidal cell populations such as CST (7). However, the RST dominated by ipsilateral innervation has relatively small damage, and its participation in motor control is relatively increased and manifested in the patient's movement, such as the clumsy and synergic movement of the upper limbs (8, 9). Spasticity after a stroke occurs and diminishes in synchrony with the appearance and disappearance of these pathological movement patterns (10, 11). Although it is still not clear how the regulation of muscle tone by the two major systems is carried out, it is speculated that the loss of inhibitory regulation caused by the imbalance of CST and RST triggers the abnormal hyperactivation of the medial reticulospinal tract (mRST) (9, 11–13). This imbalance is especially pronounced in patients with severe brain lesions. Recent imaging evidence suggests that ipsilateral PMA is the advanced cortex of RST in motor control, which plays a key role in ipsilateral movement (14, 15). After cortical damage, the contralesional PMA area is hyperactivated and may trigger a weakened inhibition of the ipsilateral mRST pathway (12). Due to the persistence of severe injury, the injured CST is difficult to recover, and this persistent weakening of inhibition can be inappropriately reinforced during the neural reorganization of the contralesional RST and related cortices (1). With appropriate treatment, attenuating the hyperexcitability of this pathway *via* contralesional PMA may be a therapeutic idea to stop spasticity from exacerbating.

Limited interventions were proven effective currently in improving spasticity. The only botulinum toxin injection backed by a lot of evidence is expensive and may require multiple iterations (16). Some central modulating strategies have also been attempted to treat post-stroke spasticity. Transcranial magnetic stimulation (TMS) is one of the options. However, ambiguity in research results leads to the disapproval of this technology on post-stroke spasticity (17, 18). The reason for this may be that previous study designs did not take into account the dynamic reorganization of CST/RST, and mainly focused on the promotion of motor recovery (1). Almost all studies with positive results were interventions targeting the bilateral M1 areas (part of CST) (19–21), improvement in spasticity accompanied by significant motor recovery. This can be interpreted as a weakening of RST regulation by enhancing CST control, which may not the most direct way to regulate spasticity-related pathways. Moreover, the traditional inhibitory TMS therapy developed based on the theory of hemispheric inhibition (22) was insufficient to reverse cortical excitability in all subjects or produced short-lived or variable results (23). Continuous theta burst magnetic stimulation (cTBS) is a novel patterned protocol of TMS, it can induce long-term depression (LTD) effect on cortical excitability and lead to long-term therapeutic benefits in facilitating induction of neuronal plasticity mechanisms (24). TBS has the advantages of shorter stimulation duration, low stimulation pulse intensity, longer post-acting time, and probably improved efficiency compared with ordinary rTMS, which is regarded as a very promising therapy (25). In addition, how to assess post-stroke spasticity objectively also set a barrier for related research. Most previous studies of TBS on post-stroke spasticity mainly use the modified Ashworth scale (MAS) as their primary outcome (18), which only roughly reflects changes in spasticity, and does not benefit mechanistic exploration.

Combined with the recent mechanism research on post-stroke spasticity, we propose a novel central regulatory target for cTBS treatment of post-stroke spasticity, namely cPMA. At the same time, the contralateral M1 area, which was extensively used in previous studies, was also introduced into our study design. Based on a sham control, we will explore the effects of “direct” intervention (cTBS *via* cPMA) and “indirect” intervention (cTBS *via* cM1) on post-stroke spasticity and verify our hypothesis on the abnormal neural regulation of spasticity after stroke.

In addition to clinical assessment scales, we will introduce neurophysiological examinations and diffusion tensor imaging (DTI) for this study. Motor evoked potentials (MEP), startle reflexes (SR), and H reflex will be used to assess the excitability of the subject's motor cortex, reticulospinal pathway, and spinal motor neurons, respectively. DTI will be performed to show the contralesional neural reorganization.

We hypothesize that cTBS in cPMA ameliorates spasticity in patients with severe subacute stroke by inhibiting the overactivated mRST and reducing the excitability of spinal motor neurons, thereby improving motor outcomes of the upper extremity. This study aims to evaluate the efficacy of cTBS therapy in the contralesional PMA for severe post-stroke spasticity and confirm the above hypothesis.

## Methods and analysis

### Study design

The study will be a non-blinded pilot randomized controlled trial with three parallel groups. The study will be performed in accordance with the Declaration of Helsinki. This protocol follows the Consolidated Standards of Reporting Trials (CONSORT) Statement on randomized trials and it will be conducted according to the Recommendations for Interventional Trials (SPIRIT). The trial was registered in the Chinese Clinical Trial Registry (No. 2200060885). It will be carried out in the Department of Rehabilitation Medicine of Tongji Hospital in Wuhan, China. A flowchart overview of the study is presented in Figure 1. The Standard Protocol Items: SPIRIT table for enrolment, interventions, and assessments is presented in Table 1. Forty-five eligible subjects will be randomly allocated into three groups equally: (1) sham-cTBS group, (2) cTBS-cM1 group (cTBS targeting contralesional M1), (3) cTBS-cPMA group (cTBS targeting contralesional PMA).

**Figure 1 F1:**
[figure not shown]
The flow diagram for this study. MEP, motor evoked potential; MAS, modified Ashworth scale; FMA-UE, Fugl-Meyer Assessment of Upper Extremity Scale; SR, startle reflex; DTI, diffusion tensor imaging; Hslp/Mslp, the ratio of the slope of H and M-waves; Hmax/Mmax, the ratio of the maximum of H and M-waves.

**Table 1 T1:** Tabulation of enrolment, interventions, and assessments throughout the trial.

	**Study period**					
	**Enrolment**	**Allocation**	**Before and after the first intervention**	**Intervention**	**Post-intervention assessment**	**Follow-up**
Timepoint	−1 week	0	1 day	0–4 week	4 week	8 week
**Enrolment**						
Eligibility screen	**×**					
Informed consent	**×**					
Allocation		**×**				
**Interventions**						
sham-cTBS group				**×**		
cTBS-cM1 group				**×**		
cTBS-cPMA group				**×**		
**Assessments**						
MAS		**×**			**×**	**×**
FMA-UE		**×**			**×**	**×**
MEP			**×**		**×**	**×**
SR			**×**		**×**	**×**
Hmax/Mmax			**×**		**×**	**×**
Hslp/Mslp			**×**		**×**	**×**
DTI		**×**			**×**	

Tabulation of enrolment, interventions, and assessments throughout the trial. cTBS, continuous theta burst stimulation; MEP, motor evoked potential; MAS, modified Ashworth scale; FMA-UE, Fugl-Meyer Assessment of Upper Extremity Scale; SR, startle reflex; DTI, diffusion tensor imaging; Hslp/Mslp, the ratio of the slope of H and M-waves; Hmax/Mmax, the ratio of the maximum of H and M-waves.

### Participants

The inclusion criteria are as follows: (1) age 18–80 years old. (2) first unilateral stroke (cerebral infarction, primary intracerebral hemorrhage, subarachnoid hemorrhage) confirmed by MRI or CT within 6 months before enrolment. (3) Perceptible muscle spasticity with MAS score >1. (4) Severe motor impairment with the Fugl-Meyer Assessment of Upper Extremity (FMA-UE) score 0–35 (9, 26). (5) Failure to induce MEP in the upper extremity of the hemiplegic side (27, 28). (6) Mini-Mental State Examination (MMSE) score ≥ 22 and compliance with the interventions. (7) sign the informed consent.

The exclusion criteria are as follows: (1) more than one stroke (patients with previous transient ischemic attack could participate), bilateral cerebral hemisphere lesion. (2) history of seizures or seizures after stroke, severe skull fracture. (3) conditions unsuitable for TBS (29), e.g., intracranial implants, cardiac pacemakers or pregnancy, implanted drug pumps, etc. (4) Medications (such as lignocaine, penicillins, cephalosporins, amphotericin, tricyclics, selective serotonin reuptake inhibitors, azatadine, aminophylline, bupropion, imipramine, clozapine, olanzapine, etc.) that may lower the seizure threshold have been used continuously for nearly 3 months. (5) serious impairments of heart, lung, liver, kidney, and other organs, cannot tolerate training. (6) participation in other spasticity rehabilitation studies.

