### Randomization and blinding

The physician will screen out the patients who meet the eligibility criteria, explain the whole content of the trial and ask the consent to sign the informed consent. Their demographic information, medical history, and medication details will then be collected. We will use an electronic random sequence generator (www.random.org) to randomly assign all of the individuals to one of the three groups in a 1:1:1 ratio. An independent researcher will conceal the allocation using sealed and opaque envelopes, numbered consecutively. In this trial, subjects, assessors, and data analysts are blind to the allocation results. Because this study involves locating therapeutic targets in the cerebral cortex, the intervenor cannot be blind. The treatment and outcome evaluation regimen are depicted in Table 1.

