### Outcome measurements

The primary outcomes are MAS and FMA-UE. Changes before and after the 4 weeks of treatment will be used as the primary measure to assess improvement in spasticity and abnormal movement synergies (9). And the secondary outcomes are results from neurophysiological examinations including H reflex, M response, MEP and SR, and changes of neuroimaging with DTI.

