### Sample size calculation

Sample size is estimated through software G^*^Power 3.1 (50). We used MAS as the primary outcome for the calculation of the effect size. It is determined to be 12 per group based on a power of 0.8 with α level at 0.05. According to a previous study (21), effect size *d* = 0.53 was calculated based on the difference in MAS score from their main research results. Through conversion, the effect size *f* used in our study is about 0.25. Repeated measures correlation in our study is set at 0.5 to detect a moderate within-between effect of Conhen's *f* = 0.25. Considering a drop-out rate of 20%, we aim to recruit totally 45 stroke subjects.

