### Statistical analysis

The SPSS 21.0 program will be used for all statistical analysis and the significance level set for all the analysis will be *P* ≤ 0.05. The Shapiro-Wilk test will be used (*P* > 0.05) to check normality. In this study, Continuous variables will be expressed as mean with standard deviation and median for non-normal distributions and categorical variables will be presented as percentage or frequencies. Between the three groups, data will be first compared using Student's *t*-test for continuous variables and the chi-square or Fisher's exact tests for categorical variables. Appropriate metrics will be processed further using repeated measures ANOVA. Bonferroni correction method and False Discovery Rate <5% will be considered for multiple comparisons. All analyses will be done with the intention to treat principle, and missing data will be estimated using multiple imputation. The mean comparisons for related outcomes in two different moments will be studied with the Wilcoxon-signed rank test. The major strategy for dealing with missing data will be a sensitivity analysis and weighted estimating equations.

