## Discussion

The motor recovery after stroke follows a basically predictable pattern, from flaccid, spastic to recovered (4, 10). In patients with severe stroke, motor function may be arrested at a certain stage limited by spasticity for a long time in the process of motor recovery (4), which is a thorny problem in the rehabilitation process. Motor rehabilitation relies on a complex combination of spontaneous recovery and motor learning to promote neural plasticity (11, 51). The spinal plastic change relates to the severity of cortical damage and has a time-limited window, almost entirely in the first weeks (52, 53). The anatomical structure determines that in patients with severe stroke, CST is more vulnerable to damage, ultimately leading to the facilitatory medial RST being unopposed and independent of cortical control (13), which plays a significant role in spasticity. Spasticity reflects a phenomenon of maladaptive neuroplasticity in motor control pathways (12), and can easily develop if there is not appropriate intervention to regulate in the course of recovery (54).

Non-invasive magnetic stimulation is a promising therapy option for modulating neural plasticity, but the undetected MEP (27) and the extensive recombination of the cerebral cortex (55) after severe stroke lead to doubtful targeting in the cortex for treatment. Although there is weak-grade evidence to support that the contralesional TMS targeting cM1 improves post-stroke spasticity, the effect is inconclusive (54). Exploring the spasticity mechanism in severe stroke patients may be more helpful to obtain optimized intervention targets and clarify the effect of this non-invasive treatment.

As mentioned previously, spasticity is thought to be a top-down manifestation resulting from hyperexcitability of the advance central PMA and its corresponding descending pathway of medial RST (12). This study will compare the acute and short-term effects of cTBS over cPMA and M1 in severe stroke patients. Moreover, we aim to demonstrate that the hyperexcitable cPMA after stroke is the cortical manifestation causing spasticity, and reducing the hyperexcitability of cPMA may help to down regulating the excitability mRST of hemiplegic side and to facilitate adaptive neuroplasticity of RST in spasticity relief and motor recovery.

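### The primary analysis as described leaves out time since stroke, although entry is open to 6 months and the endpoint is a 4-week change; adjusting for it is nearly free and protects precision.

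*Protocol article*

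**What the plan says.** - **Entry** (Participants): a first unilateral stroke "confirmed by MRI or CT within 6 months before enrolment". No minimum time is given. MAS above 1, FMA-UE 0-35 and no inducible MEP on the hemiplegic side are also required.
- **Primary measure** (Outcome measurements): "Changes before and after the 4 weeks of treatment will be used as the primary measure", applied to MAS and FMA-UE.
- **Allocation** (Randomization and blinding): an electronic generator is used to "randomly assign all of the individuals to one of the three groups in a 1:1:1 ratio", with concealment in envelopes. No stratification factor is named.
- **Analysis** (Statistical analysis): t-tests for continuous variables between the groups, then "Appropriate metrics will be processed further using repeated measures ANOVA". No covariate is named.
- **Natural course** (Discussion): motor recovery passes through flaccid, spastic and recovered stages and depends partly on spontaneous recovery. Spinal plastic change depends on the severity of cortical damage and "has a time-limited window, almost entirely in the first weeks".
- **Size** (Sample size calculation): "It is determined to be 12 per group based on a power of 0.8 with α level at 0.05", raised to 45 in total for 20% drop-out, which is 15 per arm.

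**The concern.** The article describes a recovery process that depends on time, and then measures change over a fixed 4 weeks in patients who may enter early or late in that process. If early patients change more (or less) than late ones without stimulation, time since stroke is prognostic for the primary outcome.

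Two things follow when the analysis ignores it. First, variation due to time stays in the error term and widens every between-arm interval. Second, in a trial of this size one arm may by chance sit earlier after stroke than another, and the unadjusted estimate in that trial is then shifted by the difference in spontaneous change. The shift can flatter an active arm or hide an effect.

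**Working it through.** **1. The plan's own size.** Inputs from Sample size calculation: f = 0.25, repeated-measures correlation 0.5, α = 0.05, power 0.80. There are three arms (k = 3) and three clinical assessments (m = 3: baseline, 4 weeks, 8 weeks). For the within-between interaction, λ = f²·N·m/(1 − ρ), with df (k − 1)(m − 1) and (N − k)(m − 1). At N = 36, λ = 0.0625 × 36 × 3/0.5 = 13.5 on 4 and 66 df, and power is 0.82. At N = 33 it is 0.78. So 12 per arm reproduces, and 36/0.8 = 45. The size is not in dispute; it sets the scale for chance imbalance.

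**2. How large a chance imbalance is plausible.** The documents give no distribution of time since stroke, so two are assumed. The SD of a uniform distribution is range/√12, and the SE of a difference between two arm means is SD·√(2/n). The probabilities come from simulated simple randomisations.

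| Assumed range (weeks) | n per arm | SD | SE of difference | Some pair differs by ≥ 4 weeks | Sham v cPMA differs by ≥ 4 weeks |
|---|---|---|---|---|---|
| 0-26 | 15 | 7.51 | 2.74 | 31% | 14% |
| 0-26 | 12 | 7.51 | 3.06 | 39% | 19% |
| 4-26 | 15 | 6.35 | 2.32 | 20% | 8% |
| 4-26 | 12 | 6.35 | 2.59 | 27% | 12% |

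A right-skewed distribution (exponential, mean 8 weeks, capped at 26) gives 25% for some pair at 15 per arm.

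**3. What an imbalance does to the estimate.** Let r be the correlation between time since stroke and the 4-week change. The documents give no value, so a range is shown. A 1-SE imbalance shifts an arm contrast by r·√(2/15) = 0.365r, in SDs of change. The comparison with d = 0.53 (Sample size calculation) is approximate, because the article does not say which SD underlies that d.

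| r (assumed) | Shift (SD) | Share of 0.53 | Residual variance removed (r²) |
|---|---|---|---|
| 0.1 | 0.04 | 7% | 1% |
| 0.2 | 0.07 | 14% | 4% |
| 0.3 | 0.11 | 21% | 9% |
| 0.5 | 0.18 | 34% | 25% |

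**4. Error rate and power.** In 20,000 simulated two-arm comparisons of 15 v 15 (time uniform, linear relation):

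- With no true effect, the unadjusted test rejects in about 5% of all trials at every r tried (0 to 0.7). It is valid on average.
- In the subset where the two arms differ by more than 0.5 SD in mean time (0.5 × 7.51 = 3.8 weeks on the 0-26 range), the unadjusted test rejects in 7% at r = 0.3 and 11% at r = 0.5. The adjusted test stays at about 5%.
- With a true effect of 0.53 SD, power unadjusted versus adjusted is 0.29 v 0.30 at r = 0.3 and 0.30 v 0.36 at r = 0.5. At r = 0 adjustment costs about one point (0.29 v 0.28).

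**The case against.** The strongest reply is that the design already deals with natural course. There is a randomised concurrent sham arm, expected time since stroke is equal across arms, and the p-value allows for chance imbalance. This stands, and step 4 confirms it. A reader might infer that the trial cannot tell a cTBS effect from spontaneous recovery, or that the comparison is biased. The documents do not support that.

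The cited passages are also narrower than they may look. The Discussion speaks of spinal plastic change; it does not say that change in MAS or FMA-UE is confined to the first weeks. It adds that severe patients may stay at one stage for a long time, which argues against a steep time gradient in this population. The Introduction's remark that spasticity improves in most patients, "but that of some patients with severe injury will progress in the opposite way", contrasts mild-to-moderate with severe stroke, not early with late. So a large difference in expected change between an early and a late entrant is an inference. This stands too, and it is why small values of r are shown.

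MAS above 1 at entry makes very early enrolment less likely, so the 0-26 week range is probably too wide. The 4-26 week row allows for this.

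Finally, a condensed article may leave covariates and block or stratum details to a fuller document. A reader might infer that the allocation is known to be unstratified, but the article only names no factor. The point therefore does not rest on missing allocation detail. It rests on the analysis as stated, which is unadjusted, combined with an open time window and a 4-week change endpoint.

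**Conclusion.** The point holds as one of precision and of protection against chance imbalance. It is not a finding of bias. With 15 per arm, a difference of at least 4 weeks in mean time since stroke between some pair of arms has a probability of about 20-31% under the two uniform ranges assumed.

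What that does to the result depends on r, which is unknown. At r = 0.1-0.2 the effect is minor, and at r = 0.3 the power gain from adjustment is negligible. At r = 0.5 a 1-SE imbalance moves the contrast by about a third of the planned effect, and adjustment removes a quarter of the residual variance. The case for acting is that the change costs almost nothing across this whole range, not that harm has been shown.

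**What to change.** Prespecify time from stroke to randomisation as a covariate in the primary between-arm models for MAS and FMA-UE, together with the baseline score. Because the article places plastic change early, use a scale that allows for a non-linear relation, for example log time, rather than a straight line in weeks. Fix the form before any unblinded data are seen. Report time since stroke by arm in the baseline table.

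The cost is one or two degrees of freedom. No new data, visits or patients are needed, since stroke timing is checked for eligibility and medical history is collected before assignment. The covariate can be added even if enrolment has begun.

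Stratifying the allocation by time since stroke is an optional extra. It would need one envelope series per stratum and can apply only to patients not yet randomised.
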